#### Cost-effectiveness analysis

We will perform a cost-utility analysis in accordance with the Dutch guidelines for economic evaluations in health care (*Zorginstituut 2016*) from the societal and the health care perspective. A cost (EUR) and outcomes (quality-adjusted life-year) comparison between the FFRct and the usual care groups as observed in the RCT for the 1‑year time frame will be made. Next, a state-transition model will be built to calculate the cost-effectiveness of FFRct considering a long-term time horizon. In this model we will synthesise data from the RCT with the post-hoc results of FFRct in the usual care group and literature data.

### Trial structure, registration and organisation

The study complies with good clinical practice in accordance with the Declaration of Helsinki and the laws and regulations applicable in the Netherlands, including the General Data Protection Regulation, as the clinical trial has been approved by the appropriate Medical Research Ethics Committee and Review Board (Erasmus MC, MEC-2021-0189). The clinical trial was registered under number NL76830.078.21 (NCT05174247, clinical trial registration number) on 29 December 2021. The trial started enrolment on 28 July 2021.

## Discussion

This multicentre, randomised clinical trial will evaluate the impact of adding the FFRct analysis to CCTA in the diagnostic pathway of stable chest pain patients with CCTA-derived stenosis on the rate of unnecessary ICA, cost-effectiveness, quality of life, and clinical outcomes from a Dutch perspective.

FFRct is a non-invasive technique that may change the way stable angina is diagnosed and managed. Patients who undergo ICA after CCTA often do not have a haemodynamically significant stenosis, which leads to 28–41% unnecessary ICAs in the Dutch population [16, 17]. By deriving coronary physiology from CCTA data, FFRct can be used to increase the diagnostic yield of the CCTA and, consequently, reduce the number of unnecessary ICAs as well as costs [13, 14].

In addition, FFRct may add to a proper selection of patients who may benefit from a revascularisation procedure [13]. FFRct has been validated against invasive FFR, which is an essential invasive procedure guiding revascularisation in stable CAD by investigating the haemodynamic significance of epicardial coronary stenoses (FAME trial) [9–11, 19]. Although ICA with FFR could be performed in the management of patients with stable chest pain, the invasive approach has its challenges; not only the complications inherent to invasive testing, but also the inevitable patient discomfort and costs. Determining FFR using CCTA could provide both anatomical and physiological assessment of the coronary circulation without cardiac catheterisation.

To evaluate the impact of FFRct in the FUSION trial, selection of an appropriate target population is necessary. Given the high negative predictive value of CCTA, only little added benefit of FFRct is expected in patients without suspected obstructive disease on CCTA. On the other hand, functional evaluation is also not required in case of a very high grade stenosis (> 90%) on CCTA, because the probability of this stenosis to be haemodynamically significant on ICA is very high [8, 20]. Therefore, we will only include patients with a 50–90% stenosis on CCTA.

Similar to the design of the CRESCENT trial [17], the FUSION trial design is based on improving the diagnostic strategy of stable angina pectoris patients and not merely on identifying which diagnostic test is superior. In the FUSION trial, we focus on patients in whom we expect FFRct to be most appropriate, namely patients with intermediate anatomic stenosis. On top of that, we have designed our study in such a way that we can estimate the number of false negative FFRct results and determine the effects of missing CAD diagnosis, by performing a post-hoc FFRct analysis in the control group based on the existing CCTA in each patient. The patients in the control group undergo routine care, which is not based on FFRct but, mostly, on ICA. This ensures that we can determine how often the FFRct results would have led to a false negative result. In the intervention group, patients with FFRct > 0.80 will include both the true and false negatives, and we will assess the outcome of these patients. These results combined will provide solid data on how often false negatives occur and what the consequences are. We will be able to make an assumption on the maximum risk these patients have for developing major adverse cardiac events in 1 year.

Major adverse cardiac events is not selected as the primary endpoint, as it would require a very high number of patients to be included in the trial. Since we can make accurate assumptions of the risk of major adverse cardiac events in the study population—and unnecessary ICAs is a clinically relevant endpoint—we have chosen the latter as the primary endpoint.

The FUSION trial has been designed to investigate the role of FFRct in the diagnostic strategy of patients with stable chest pain after CCTA and does not have the potential to answer questions about optimal treatment strategy in patients with symptomatic CAD. This was subject of the ISCHEMIA trial, which results support that the vast majority of patients with CAD (in a selected population of patients with an abnormal functional test) can be treated with an initial conservative strategy of medical therapy alone [21]. These results do not undermine the prominent role of functional testing in the management of stable chest pain patients, whether this should be based on functional testing or based on FFR testing, such as in the FUSION trial.

First of all, it remains useful to confirm a clinical diagnosis in patients with quality-of-life-limiting symptoms. Secondly, as the ORBITA trial demonstrated, having symptoms and an anatomic stenosis is insufficient to detect the patients for whom revascularisation will improve quality of life [22]. On top of that, ISCHEMIA targeted a specific patient population, as most patients referred for further testing in the current era would have been too low risk to be included in the trial, but also high-risk patients (unacceptable level of angina despite maximal medical therapy, left main disease on CCTA, ejection fraction < 35%) were excluded [21].

In conclusion, the FUSION trial is designed to evaluate whether the use of FFRct could decrease unnecessary ICA in patients with stable chest pain in both academic and peripheral hospitals with multiple CCTA vendors. The FUSION trial aims to provide a new strategy in Dutch health care for the diagnostic workup of stable chest pain. As the FUSION trial is part of the research programme ‘Potentially Promising Care’ of the Dutch National Health Care Institute, the results of the study will be used for a fast-track procedure to assess if FFRct reimbursement can be included in the standard health care package.

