#### Post-hoc FFRct analysis in usual care group

Since in the intervention group, patients with FFRct > 0.80 will in principle not undergo ICA, false negative FFRct cases remain unidentified. Therefore, FFRct will also be performed in the usual care group (post-hoc FFRct), but will neither be revealed to the clinical site nor influence the diagnostic pathway. The treating clinician will be blinded to these FFRct results. This way, we can indirectly gauge the number of false negative FFRct findings retrospectively in patients who underwent ICA in the control group without influencing patient management in this group. A false negative is defined as negative FFRct result with an ICA showing haemodynamically significant stenosis on invasive FFR.

Data to be collected at baseline, 90 days and 1 year are presented in Electronic Supplementary Material.

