### Study endpoints

The primary endpoint is the rate of unnecessary ICA occurring within 90 days in both groups as determined on a per patient level. Unnecessary ICA is defined as any ICA without haemodynamically significant CAD. The leading indicator for the evaluation of significant CAD is the functional measurement (FFR/iFR). If functional measurements are not available, then significant CAD is indicated by quantitative coronary angiography. Primary and secondary endpoints definitions are listed in Fig. S2 in Electronic Supplementary Material.

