### Statistical analysis

#### Sample size calculation

We estimate that 28–41% of the patients who undergo ICA after CCTA do not have a haemodynamically significant stenosis [16, 17]. With the addition of FFRct we expect that the number of unnecessary ICA procedures will decrease by 33%. To reach an 80% power, a 0.05 significance level, and assuming a 10% drop-out rate, 528 patients need to be included in the trial (264 in each group).

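### The stated method for judging the consequences of a negative FFRct has no comparator, although FFRct > 0.80 is a baseline stratum that can be compared between the randomised arms.

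*Protocol article*

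**What the plan says.** All places are in the protocol article.

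- **Study procedures, intervention group:** FFRct is computed in all patients from the available CCTA. Those with FFRct > 0.80 are in principle managed conservatively.
- **Post-hoc FFRct analysis in usual care group:** "FFRct will also be performed in the usual care group (post-hoc FFRct), but will neither be revealed to the clinical site nor influence the diagnostic" work-up. The stated purpose is to gauge the number of false negatives among controls who underwent ICA. A false negative is a negative FFRct with a significant stenosis on invasive FFR.
- **Study endpoints:** "Unnecessary ICA is defined as any ICA without haemodynamically significant CAD". The primary endpoint is the per-patient rate of such procedures within 90 days.
- **Data analysis:** primary and secondary outcomes are analysed by intention to treat, with similar models for the secondary endpoints.
- **Cost-effectiveness analysis:** the control-arm FFRct results also feed the long-term model.
- **Discussion:** the intervention-arm patients with FFRct > 0.80 "will include both the true and false negatives, and we will assess the outcome of these patients". Taken together with the control-arm count, this is presented as solid evidence on how frequent false negatives are and what follows from them. The section adds: "We will be able to make an assumption on the maximum risk these patients have for developing major adverse cardiac events in 1 year".

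No comparison of outcomes between the FFRct-negative patients of the two arms is stated.

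**The concern.** A consequence of deferral is an effect, and an effect needs a contrast. A low 1-year event rate in FFRct-negative intervention patients could mean that deferral is safe. It could equally mean that such patients have few events however they are managed. The control-arm false-negative count does not settle this. It covers only patients selected for ICA, and their disease was found, so they do not show what happens when disease is missed.

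The primary endpoint does not fill the gap. An avoided ICA that would have shown significant CAD leaves the count of unnecessary ICAs unchanged, so missed disease is not penalised. The whole-arm secondary analyses are randomised, but they mix in FFRct-positive patients, who should go on to ICA in the intervention arm, and so dilute any effect of deferral.

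The results are meant to inform a reimbursement decision, so the evidence on deferral carries weight.

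**Working it through.** **1. The plan's own figure.** The only computed figure is the sample size of 528. It rests on "To reach an 80% power", "a 0.05 significance level, and assuming a 10% drop-out rate", a control rate in the 28–41% range and a 33% relative reduction. With an assumed control rate of 35%, against 0.35 × 0.67 = 23.45%, the unpooled two-sided formula gives 240 per arm, and 240 × 1.1 = 264. The figure is reproduced, but it concerns the primary endpoint only and does not bear on this point.

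**2. Is FFRct > 0.80 a baseline stratum?**
- A CCTA stenosis is an inclusion criterion, so the scan precedes randomisation.
- FFRct is computed from that scan in all intervention patients and, according to the Discussion, in each control.
- In controls the result is withheld from the site and cannot alter management.

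FFRct status is thus a function of pre-randomisation data in both arms. A comparison by randomised arm within FFRct > 0.80 is protected by the randomisation, provided that FFRct is processed alike in both arms. It estimates what results from disclosing a negative FFRct, including the deferral that follows.

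**3. What each stated source can show.**

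| Source | Who | Contrast? |
|---|---|---|
| False-negative count | Controls who had ICA | No; selected, and disease found |
| Outcomes with FFRct > 0.80 | Intervention arm only | No; true and false negatives mixed |
| Secondary endpoints by arm | All randomised | Yes, but diluted by FFRct-positive patients |

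**4. Likely size of the stratum (assumption).** The documents do not give the FFRct-negative share. Their nearest inputs are sensitivity 80–88% and specificity 61–86% (Background, per vessel), and the statement that "28–41% of the patients who undergo ICA after CCTA do not have a haemodynamically significant stenosis" (Sample size calculation). Suppose that these applied per patient to everyone randomised. With p = 1 − 0.41 to 1 − 0.28 = 0.59 to 0.72:

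share = p(1 − sens) + (1 − p)spec

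- Lowest: 0.72 × 0.12 + 0.28 × 0.61 = 0.257, and 0.257 × 264 ≈ 68 per arm.
- Highest: 0.59 × 0.20 + 0.41 × 0.86 = 0.471, and 0.471 × 264 ≈ 124 per arm.
- After 10% drop-out: about 61 to 112 per arm.

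**5. Precision without drop-out.**
- Zero events in one arm, one-sided 95% upper bound: 1 − 0.05^(1/n) = 4.3% (n = 68) and 2.4% (n = 124).
- Between-arm difference at an assumed 2% MACE rate in both arms: 1.96 × √(2 × 0.02 × 0.98 / n) = 4.7 points (n = 68) and 3.5 points (n = 124).

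**6. Power for MACE under wider assumptions.** With 30–60% FFRct-negative among about 237 evaluable patients per arm (71–142) and a MACE rate of 1–5%, the power to detect a doubling is 7–36%, and the half-width is 2.3–7.2 points.

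**The case against.** **The article is condensed.** The sentences at issue are rationale in a Discussion. A subgroup contrast could stand in the analysis plan, and the endpoint definitions are in a supplement that is not shown. This limits the point: the comparison is unstated, not excluded, and no figure is wrong. But the article does set out a method for judging the consequences of false negatives and claims that it suffices. That claim can be assessed as written, and it does not follow.

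**Control-arm FFRct is used.** This is true. It serves the false-negative count and the cost-effectiveness model, and clinical outcomes are compared between whole arms. A reader might infer that safety is judged from the intervention arm alone, or that the randomised information is thrown away. The documents do not support either reading.

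**The endpoint does not reward every avoided ICA.** A reader might infer that it does. It counts only procedures without significant CAD, so an avoided ICA that would have shown disease neither lowers nor raises the count. If the rate were taken per ICA performed, avoiding such a procedure would even raise it. What stands is the narrower point that missed disease is not penalised when patients are counted.

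**MACE will be imprecise.** This stands. The Discussion itself says that MACE as the primary endpoint would need very many patients. Imprecision is a reason to show the interval, and it affects the single-arm figure too.

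**Conclusion.** The point holds as a cheap improvement to a stated method, not as an error in a figure. Followed as written, the combination described in the Discussion cannot isolate the effect of deferring ICA on a negative FFRct, and a randomised contrast within FFRct > 0.80 is available from data already planned.

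The size is approximate. About 26–47% FFRct-negative (68–124 per arm, or 61–112 after drop-out) rests on applying per-vessel accuracy and a figure for patients undergoing ICA to all randomised patients. On that footing, and before drop-out, even zero events in one arm would leave a one-sided 95% upper bound of about 2.4–4.3%. The between-arm difference at an assumed 2% MACE rate would carry a half-width of about 3.5–4.7 points. It would be too much to expect this comparison to prove deferral safe or unsafe; for MACE it gives an estimate with a wide interval. Outcomes that occur more often than MACE should be more informative.

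**What to change.** - State that 1-year outcomes in patients with FFRct > 0.80 will be compared by randomised arm, as risk or mean differences with 95% confidence intervals: MACE, ICA with significant CAD, revascularisation, quality of life and cost.
- State that FFRct is processed identically in both arms, blind to allocation and outcome, with one rule for classing a patient as negative.
- Express the maximum risk as an upper 95% confidence limit, and give the number of patients behind it.
- Label the analysis as estimation, not as a confirmatory safety test.
- If the analysis plan already contains this comparison, bring the Discussion wording into line with it.

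The cost is a few added tables, with no extra patients, scans or follow-up. The downside is wide intervals that have to be shown. The change should be fixed before results by arm are seen, since afterwards the comparison would be post hoc.
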